### Sample Size and Power Calculation

Based on a feasibility study performed at PCH ED before the multicenter study [43], we estimate a true appendicitis rate of 30% in the multicenter study, and that all the CPSs will be calculable in at least half of the patient cohort. We aim to have a sample size of 2400 children with undifferentiated abdominal pain enrolled, which will result in all CPSs being calculable in a minimum of 360 enrolled cases of true appendicitis. This will provide a level of precision such that a 95% CI around the AUC will range from 0.016 for an AUC estimate of 0.95-0.032 for an AUC point estimate of 0.75 [67]. It will also provide more than 85% power for a 2-sided test, with α=.05, to find a difference of .05 between 2 AUCs if both values are ≥0.80, assuming the correlation of risk scores amongst appendicitis cases and that amongst noncases have an average of at least 0.5 [68]. Under this same assumption, if both AUC values are ≥0.9, the planned sample numbers would provide more than 90% power to detect a difference of 0.04.

### Statistics and Interim Analysis

We will follow Standards for the Reporting of Diagnostic accuracy studies (STARD) 2015 guidelines for statistics [69] and the Strengthening the Reporting of Observational Studies in Epidemiology (STROBE) guidelines [70], and validation of CPSs will be performed and reported in according to the 2014 updated methodologic standards for interpreting clinical decision rules in emergency medicine [71]. The AUC will be calculated for the various published CPSs and the clinician's gestalt for the outcome of appendicitis. The sensitivity, specificity, negative predictive value, positive predictive value, negative likelihood ratio, positive likelihood ratio, and missed appendicitis rate will be calculated based on the published cutoffs for each score [2-31]. For the pARC, subanalysis will be performed for the following pARC categories based on previous validation studies [4,56]: ≤5%, 6%-15%, 16%-25%, 26%-50%, 51%-75%, 76%-90%, and >90% for pediatric EDs and <5%, 5%-14%,15%-24%, 25%-49%, 50%-74%, 75%-84%, and ≥85% for mixed ED. For clinician’s gestalt, subanalysis will be performed for each point on the Visual Analog Scale. The AUC will also be calculated for complex appendicitis to assess the optimal cutoffs for each CPS to detect complex appendicitis.

The best-performing CPS will be identified by the highest AUC. Sensitivity and positive predictive value will be calculated to establish the CPS’s ability to identify high-risk patients, and the misclassification rate (proportion of patients identified as low-risk who had acute appendicitis) and negative likelihood ratio will be calculated to establish the CPS’s ability to identify low-risk patients. Accuracy will be reported as the proportion of patients not misclassified as either low-risk or high-risk as defined by published cutoffs. Baseline analyses of patient characteristics based on the risk groups as calculated by the best-performing CPS will be conducted by presenting simple counts and percentages with interquartile ranges.

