### Strengths and Limitations

Our study will allow the simultaneous comparative application and validation of 30 CPSs for diagnosing pediatric appendicitis outside their derivation settings. In addition to a high recruitment rate, the study will depend on high follow-up rates to ensure that our results accurately represent the whole population of children presenting to the ED with suspected appendicitis, as all patients lost to follow-up will be excluded from data analysis for CPS calculation. Ideally, all patients with abdominal pain would undergo investigations or appendectomy to determine the presence or absence of appendicitis; however, this would increase the rate of unnecessary investigations and potentially the rate of negative appendectomies should investigations be inconclusive. Therefore, a similar methodology to a previous PREDICT study looking at clinical decision rules for head injuries [72] was adapted using follow-up telephone or email contact to establish the presence or absence of appendicitis after discharge from the ED. It is also possible some patients with appendicitis would be treated conservatively with antibiotics and excluded from the study; however, this would represent a small number of patients as this is an uncommon practice in ANZ with only one patient in the feasibility study treated conservatively after a radiological diagnosis of appendicitis due to parental preference [43].

The predictor variables for the 30 CPSs were derived solely from original publications [2-31] and amalgamated into a single case report form developed by the study authors, which may introduce an element of interpretation in terms of the exact clinical terminology used in ANZ ED settings. The difficulty and variability of prospective clinician data collection in busy EDs in completing the case report form may result in a significant proportion of patients with multiple missing variables to calculate all CPSs; however, the feasibility study demonstrated the viability of the case report form used with all study CPSs being calculable in the majority of the patient cohort (ranging from 52% to 93.3%) based on constituent variables available [43]. Implementation of an appropriate method, such as multiple imputation, will be considered to minimize potential biases that may arise from missing data in the multicenter study [73].

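### The best score is named by the highest AUC point estimate among 30, with no paired comparison and no common set of children in the rule, so small true differences can be ranked by chance or by who could be scored

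*Protocol article*

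**What the plan says.** All references are to the Protocol article.

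- **Rule** (Statistics and Interim Analysis): "The best-performing CPS will be identified by the highest AUC". No interval, test, margin, tie rule or analysis set is attached.
- **Number of scores** (Strengths and Limitations): the study is described as a "simultaneous comparative application and validation of 30 CPSs".
- **Sizing** (Sample Size and Power Calculation): "We aim to have a sample size of 2400 children with undifferentiated abdominal pain enrolled"; "we estimate a true appendicitis rate of 30% in the multicenter study"; the authors expect that "all the CPSs will be calculable in at least half of the patient cohort", leading to "all CPSs being calculable in a minimum of 360 enrolled cases of true appendicitis". The section then gives the 95% CI precision of one AUC, and the power of a two-sided 5% test between two AUCs with an assumed average score correlation of at least 0.5.
- **Missing items** (Strengths and Limitations): the feasibility study is reported as having "all study CPSs being calculable in the majority of the patient cohort (ranging from 52% to 93.3" percent). For the multicenter study, "Implementation of an appropriate method, such as multiple imputation, will be considered".
- **Use of the winner**: baseline characteristics are tabulated by its risk groups (Statistics and Interim Analysis), clinician gestalt is compared with it (Strengths and Limitations), and its implementation in the region's EDs is foreseen (Abstract, Conclusions).

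**The concern.** The rule and the sample-size section do not meet. The study is sized to compare two AUCs in a paired way and to give each AUC an interval, but the sentence that names the winner uses neither. Taking the largest of 30 correlated estimates treats any observed lead, however small, as decisive.

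Nor does the article say which children the ranked AUCs come from. If each score is assessed wherever its own items happen to be recorded, the scores are assessed in different children. An AUC depends on case mix, so part of an observed difference could reflect who was scorable and not how well the score discriminates.

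The named score is the study's headline conclusion and is meant for clinical pathways. A single winner that is really tied with several others would be presented with more confidence than the data carry.

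**Working it through.** **1. Reproduce the plan's figures.** Cases: 2400 × 0.30 × 0.50 = 360. Non-cases: 2400 × 0.70 × 0.50 = 840.

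Hanley-McNeil: SE² = [A(1−A) + (n1−1)(q1−A²) + (n0−1)(q2−A²)] / (n1·n0), with q1 = A/(2−A), q2 = 2A²/(1+A), n1 = 360 and n0 = 840.

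- A = 0.75: q1 = 0.6000, q2 = 0.6429, A² = 0.5625. SE² = (0.1875 + 359 × 0.0375 + 839 × 0.0804)/302,400, so SE = 0.0164 and 1.96 × SE = 0.0321. The plan gives 0.032.
- A = 0.95: the same steps give 1.96 × SE = 0.0160. The plan gives 0.016.

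Paired power = Φ(difference/SE_diff − 1.96), with SE_diff² = SE1² + SE2² − 2r·SE1·SE2, where r is the correlation between the two AUC estimates. Simulation at score correlation 0.5 gives r = 0.44 for 0.80 versus 0.85 and r = 0.39 for 0.90 versus 0.94.

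- 0.80 versus 0.85: at r = 0.40, SE_diff = 0.0158 and power is 89%; at r = 0.45 it is 91%. The plan says more than 85%.
- 0.90 versus 0.94: at r = 0.40, power is 94%. The plan says more than 90%.

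The sizing is sound for the differences it names.

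**2. Two close scores.** For 0.84 versus 0.85, power is about 10% to 12%. The point estimates come out in the wrong order in 22% of runs.

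**3. The printed rule with 30 scores.** Normally distributed scores, pairwise correlation 0.5, one common set of 360 cases and 840 non-cases. The true AUCs are assumptions: one score at 0.85 and 29 lower by a fixed gap.

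| True lead over the other 29 | Truly best score ranks first |
|---|---|
| 0.01 | 19% |
| 0.02 | 56% |
| 0.03 | 86% |
| 0.05 | 99.8% |

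With true AUCs spread evenly from 0.70 to 0.85, the best ranks first in 55%. If all 30 are equal, the winner's AUC is overstated by about 0.018. If each score instead uses its own random 52% to 93% of 2400 children, the shares are 20% (lead 0.01), 61% (0.02) and 99.8% (0.05).

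**4. Different subsets.** Take a score with true AUC 0.85 that is calculable in 52% of children. The selection patterns are assumptions.

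| What decides calculability | AUC in the score's own subset | Shift |
|---|---|---|
| Random | 0.850 | 0 |
| Rises with the score, logit slope 0.5 per SD | 0.843 | −0.007 |
| Rises with the score, logit slope 1.0 per SD | 0.835 | −0.015 |
| Mostly mid-range children | 0.814 | −0.036 |
| Mostly clear-cut children | 0.878 | +0.028 |

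The extremes are 0.036/0.05 = 72% and 0.028/0.05 = 56% of the difference the study is powered to find.

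**5. Does a common set help?** Take two scores with equal true AUC 0.85, one of them calculable in 52% with selection on suspicion. At the strongest slope tried (2), the restricted score shows 0.827 in its own subset against 0.851 for the other in all children. In the same children they show 0.827 and 0.828. The spurious gap comes from comparing across subsets.

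**The case against.** Several parts of the case against carry weight.

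- **Separate subsets are not a stated plan.** A reader might infer that each AUC in this study will come from a different 52% to 93% of children. That range is from one feasibility site; for this study the article assumes at least half. The power calculation is paired, and imputation, if adopted, would put every score on the same children. Separate subsets are a likely default, no more.
- **The cause of missingness is not given.** Because children can enrol without blood tests, a reader might infer that laboratory-based scores are assessed only in the more strongly suspected. The article gives no blood-taking rate and does not say which scores were least calculable. It points to case report forms being completed in busy departments, and says most scores mix clinical and laboratory items. The shifts in step 4 are therefore illustrations of either sign, and zero under random missingness.
- **Uncertainty is not absent from the protocol.** Intervals and a two-sided comparison appear in the sample-size section; they are missing from the selection rule only.
- **The cost of a wrong pick is small.** In two further scenarios (true best 0.86 with five at 0.85 and the rest assumed at 0.70 to 0.83; and an even spread from 0.70 to 0.86), at correlation 0.5 the best is picked 50% and 57% of the time, but the chosen score falls short by only 0.005 and 0.004 on average. At correlation 0.85, which the plan's lower bound of 0.5 allows, it is picked 77% and 74% of the time, with an average shortfall of 0.002.
- **The AUC is not the only evidence.** The primary aim is to validate each score, and classification at published cutoffs is also reported.

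An analysis plan not shown may settle the imputation model and the analysis set. That does not dispose of the point: the article prints a complete selection rule, and followed as printed it declares one winner among scores the data may not separate. The chance element remains even on a single common set.

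**Conclusion.** The point holds in limited form. The selection rule ignores the paired comparison and intervals that justify the sample size, and it does not say in which children the 30 AUCs are compared. Chance can decide the winner when the true lead is about 0.03 or less; a lead of 0.05 is almost always found. These frequencies rest on assumed true AUCs, normally distributed scores and correlation 0.5, and improve with higher correlation. Differing subsets could add a shift of roughly −0.04 to +0.03, but only if calculability is informative, which the documents neither state nor exclude.

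The documents do not support saying that the ranking will be an artefact, or that the winner will be materially inferior. In the spread scenarios its AUC is overstated by no more than about 0.01, below the planned half-widths of 0.016 to 0.032. What is at risk is an unjustified claim of a single best score. The rule should be changed before analysis.

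**What to change.** Amend the selection sentence in Statistics and Interim Analysis as follows.

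1. Rank all scores on one common set: every child with a verified outcome, with missing score items multiply imputed (a model including outcome, gestalt, the other items and site).
2. As sensitivity analyses, repeat the ranking in children for whom all scores are calculable, and give each score's complete-case AUC. The first also answers the fair objection that a score needing blood results cannot be used where none were taken.
3. Report each score's paired AUC difference from the leader with a bootstrap or DeLong 95% interval.
4. Describe scores whose interval includes 0 as a leading group with the top-ranked score, and do not declare one winner on the point estimate alone.

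Requiring a multiplicity-adjusted interval to exclude 0 against all 29 competitors before any score may be called best is a debatable trade-off, and is not needed here. Power at a true gap of 0.01 is only 10% to 12% before any adjustment, so a single score would seldom qualify.

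Cost: more analysis work, a missing-at-random assumption, and possibly a leading group in place of one best score. No further recruitment or data collection is required.

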**Methods:**

This prospective multicenter observational study across 10 ANZ EDs is recruiting children 5-17 years presenting to participating EDs with acute right-sided or generalized abdominal pain lasting ≤7 days and clinician suspicion of appendicitis. CPSs will be calculated by the study team from clinician-recorded data and clinician gestalt recorded on a visual analog scale. Accuracy of CPSs will be assessed by the area under the receiver operating characteristic curve and proportions correctly identified as either low-risk or high-risk based on the CPSs published cutoffs. The final diagnosis of appendicitis will be confirmed on histopathology, and the absence of appendicitis confirmed by telephone, email, or a combination of both to follow up for those discharged directly from ED.

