**Conclusions:**

This study aims to determine the best-performing CPS for diagnosing pediatric appendicitis in ANZ EDs. Implementation of this CPS in ANZ EDs has the potential to reduce health care costs, rationalize the use of health care resources, and improve the management and outcomes of childhood appendicitis.

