## Introduction

### Background

Abdominal pain is a common reason for children to attend the emergency department (ED), with acute appendicitis being the most frequent cause requiring surgical intervention [1]. Many clinical prediction scores (CPSs) [2-31] have been developed and ED clinicians are encouraged to use CPSs to assist with determining the risk of appendicitis [32]. Most CPSs involve calculating a score based on combinations of clinical features and laboratory findings to classify patients into low-, intermediate-, or high-risk. The most frequently used CPSs in children are the Alvarado score [2], the Pediatric Appendicitis Score (PAS) [3], and the pediatric appendicitis risk calculator (pARC) [4], with each based on different sets of collected variables.

The Alvarado score is one of the most widely studied CPSs for the diagnosis of acute appendicitis in adult populations based on 8 variables with a total score of 10 [2], and it has since been studied in pediatric populations with varying results [33-44]. The PAS was developed specifically with slightly different variables for diagnosing appendicitis in children [3] and has been validated in multiple studies in various settings [42-54]. However, both the Alvarado score and PAS have been found to have limited clinical utility due to a large proportion of the scores falling into the intermediate risk group and failing to consider variability in clinical presentation based on factors such as age, sex, and duration of pain. This led to the development of the pARC score, which uses a multivariable prediction model that includes variables such as age, sex, and duration of pain to quantify the risk of appendicitis on a continuous scale [4], with promising results noted on various validation studies since its development [36,43,44,55-57].

However, few have compared multiple CPSs for pediatric appendicitis, and most existing studies are limited by the number of CPSs included [36,40,58], validated only in retrospective cohorts [59], did not include more recent CPSs such as the pARC score [40,59,60], and did not compare CPSs to clinician gestalt. Moreover, most of these studies were performed overseas with limited validation in children in Australia and New Zealand (ANZ) EDs [61]. This can result in inconsistent practice and an increasing number of children exposed to potentially unnecessary imaging and laboratory investigations.

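### The best score is named on the AUC point estimate alone, which cannot see published cutoffs or the intermediate group and cannot separate close scores

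*Protocol article*

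**What the plan says.** The rule is in the protocol article, Statistics and Interim Analysis: "The best-performing CPS will be identified by the highest AUC". No other criterion and no allowance for uncertainty is attached to it.

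Three other places bear on it.

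- The Background says that the Alvarado score and the PAS have "limited clinical utility due to a large proportion of the scores falling into the intermediate risk group".
- The Abstract (Methods) says accuracy will be assessed by AUC and by "proportions correctly identified as either low-risk or high-risk based on the CPSs published cutoffs". Statistics and Interim Analysis words the second measure differently: "Accuracy will be reported as the proportion of patients not misclassified as either low-risk or high-risk as defined by published cutoffs".
- The Abstract (Conclusions) gives finding the best-performing score as the aim and adds: "Implementation of this CPS in ANZ EDs has the potential to reduce health care costs".

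Cutoff-based measures are planned. Sensitivity, specificity, predictive values, likelihood ratios and the "missed appendicitis rate will be calculated based on the published cutoffs for each score". None of them enters the choice of best score, and the size of the intermediate group is not a named measure.

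**The concern.** AUC depends only on how a score ranks children with and without appendicitis. Moving the low- and high-risk cutoffs leaves it unchanged, however many children then fall between them. The rule is therefore blind to the property that the Background treats as the weakness of existing scores.

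It also takes the largest of 30 estimates at face value. If several scores lie close together, sampling error can decide which is named best, although the study is sized for AUC differences of 0.04 to 0.05.

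At stake is the headline result. A score could be put forward on an AUC lead the data do not support, while a real difference in the share of children given a usable low- or high-risk answer plays no part.

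**Working it through.** **Inputs.** From Sample Size and Power Calculation: 2400 children, "we estimate a true appendicitis rate of 30% in the multicenter study", and "all the CPSs will be calculable in at least half of the patient cohort". Cases = 2400 × 0.30 × 0.50 = 360; noncases = 2400 × 0.70 × 0.50 = 840.

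**The plan's own precision.** Hanley-McNeil: SE² = [A(1−A) + (n₁−1)(q₁−A²) + (n₀−1)(q₂−A²)] / (n₁n₀), with q₁ = A/(2−A) and q₂ = 2A²/(1+A). At A = 0.95, SE = 0.00819 and 1.96 × SE = 0.016. At A = 0.75, SE = 0.01637 and 1.96 × SE = 0.032. Both stated figures reproduce as half-widths. The power statements are consistent too: 86% to 93% for 0.80 v 0.85 and 93% to 97% for 0.90 v 0.94, for a correlation r between AUC estimates of 0.35 to 0.50. The sample size is not in dispute.

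**Precision of a gap between two scores.** Near A = 0.87, SE = 0.01272 for each score. The SE of a paired difference is √[2 × SE² × (1−r)].

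- r = 0.50: SE = 0.01272, half-width 0.025.
- r = 0.35: SE = 0.01450, half-width 0.028.

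The values of r are assumptions. The counts are the planned minimum. If two scores were calculable in all 2400 children, the half-widths would shrink by about √0.5, to roughly 0.018 to 0.020. In 1000 simulated studies with true AUCs of 0.86 and 0.88 and score correlation 0.5 (360 cases, 840 noncases), a paired test separated the two in 40.5%; the truly lower score had the higher estimate in 4.1%.

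**AUC and the intermediate group.** Equal-variance binormal model: noncases N(0,1), cases N(μ,1), μ = √2 × Φ⁻¹(AUC), prevalence 30%. AUC is held at 0.88 (μ = 1.662) and only the assumed cutoffs move:

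| Cutoffs (SD) | Intermediate | Accuracy as worded in Statistics and Interim Analysis |
|---|---|---|
| 0.5, 1.3 | 21.9% | 89.5% |
| 0, 1.8 | 47.7% | 96.0% |
| −0.5, 2.5 | 71.5% | 99.1% |

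That accuracy is 1 − (cases called low-risk + noncases called high-risk)/N. It rises as the intermediate group grows, and reaches 100% for a score that places every child there. The Abstract's wording, which asks for correct placement, would give that score 0%.

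**Can the ranking reverse?** Net benefit = prevalence × sensitivity − (1 − prevalence) × (1 − specificity) × t/(1−t), using the low cutoff at t = 10% and the high cutoff at t = 50%. All cutoffs, AUCs and thresholds here are assumptions.

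| Score | AUC | Sensitivity at low cutoff / specificity at high cutoff | Intermediate | Correctly placed | Wrongly placed | Net benefit 10% | Net benefit 50% |
|---|---|---|---|---|---|---|---|
| X | 0.88 | 99.5% / 99.9% | 84.9% | 14.9% | 0.2% | 0.235 | 0.022 |
| Y | 0.86 | 97% / 97% | 60.8% | 36.2% | 3.0% | 0.241 | 0.088 |
| X, same cutoffs as Y | 0.88 | 97% / 97% | 55.7% | 41.3% | 3.0% | 0.245 | 0.103 |

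The AUC rule names X. The planned accuracy also favours X (99.8% v 97.0%), although Y has the higher net benefit at both thresholds. With equal operating points the AUC leader wins throughout.

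**Would the proportion correctly placed be a safe tie-break?** A score with AUC 0.86 and a single cutoff at its Youden point has sensitivity and specificity of 77.8%. It places 77.8% correctly against Y's 36.2%, but misses 22% of cases against 3% at Y's low cutoff. Its net benefit is lower than Y's at both thresholds: 0.216 v 0.241 and 0.078 v 0.088.

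**The case against.** The strongest reply is that this is a defensible design choice. The primary aim is external validation, AUC is the measure attached to the primary outcome and to the sample size, and one prespecified criterion is objective. The Abstract lists two accuracy measures without saying that both decide the winner, so reporting both while selecting on one is not a contradiction. Many cutoff-based measures will be published, and a reader could infer a large intermediate group from low sensitivity at the high cutoff and low specificity at the low one. Cutoffs can also be moved later, whereas discrimination cannot.

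Most of this stands. What it does not answer is that none of the cutoff measures affects which score is named, that the one composite rewards a large intermediate group, and that the point estimate is used without its uncertainty.

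A reader might go further and infer that the plan will recommend a score with the failing it criticises. The document does not support that. It gives no cutoffs or score distributions, the reversal above depends on assumed and unequal cutoffs, and it vanishes when the cutoffs are equal. Nor does the document bind implementation to the AUC leader; it speaks only of potential.

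**Conclusion.** The point holds as a worthwhile improvement, not as an error that invalidates the study. Three things are established. The sole selection criterion carries no information on the published cutoffs or the intermediate share. At the planned minimum numbers, AUC gaps of about 0.025 or less near 0.87 are not distinguishable from zero, given Hanley-McNeil standard errors and a correlation between AUC estimates of 0.35 to 0.5. This does not make the ordering random: in the simulation a true gap of 0.02 was usually ranked correctly, but most studies could not exclude no difference. Third, the accuracy wording in Statistics and Interim Analysis, read literally, credits intermediate children as correct, while the Abstract's wording does not.

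That a lower-AUC score can be more useful at its cutoffs is shown only as a possibility, under a binormal model with assumed cutoffs. How often it would happen among the 30 scores cannot be computed from the document.

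**What to change.** 1. Keep AUC as the first screen. For each score, compute the paired AUC difference from the leader in children with both scores calculable. Treat scores whose 95% CI includes 0 as not distinguished by AUC. Show the number of children behind each comparison, because a score calculable in fewer children has a wider interval and stays in more easily.
2. Compare the undistinguished scores on net benefit at their published cutoffs, over thresholds that the investigators fix before analysis. The 10% and 50% used above are illustrations, not proposals. State which published category limits are used for scores reported in several bands, such as the pARC.
3. For every score, report the proportions correctly placed, wrongly placed (missed cases and false high-risk separately) and intermediate. Do not choose on the raw proportion correctly placed, which favours single-cutoff scores whatever they miss.
4. Reword the accuracy definition in Statistics and Interim Analysis to agree with the Abstract, so that intermediate children are not counted as correct.

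The cost is a few sentences of analysis text, settled before results are seen; every quantity comes from data already planned. The downside is that the result may be a small set of scores, or a winner that is not the AUC leader.

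### Read literally, the Methods definition of accuracy counts every intermediate-risk child as accurate, so the reported figure is not comparable between scores

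*Protocol article*

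**What the plan says.** Four places in the protocol article bear on this.

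- Statistics and Interim Analysis defines the measure: "Accuracy will be reported as the proportion of patients not misclassified as either low-risk or high-risk as defined by published cutoffs".
- The abstract's Methods paragraph names two ways of assessing accuracy, the AUC and "proportions correctly identified as either low-risk or high-risk based on the CPSs published cutoffs". It gives no denominator.
- The Introduction (Background) says that most scores "classify patients into low-, intermediate-, or high-risk". It describes the Alvarado score and PAS as having "limited clinical utility due to a large proportion of the scores falling into the intermediate risk group", and gives a second limitation beside it: neither score allows for differences in presentation by age, sex and pain duration.
- The selection rule is in the same paragraph as the accuracy definition: "The best-performing CPS will be identified by the highest AUC". That paragraph also defines "the misclassification rate (proportion of patients identified as low-risk who had acute appendicitis"), which covers the low-risk side only.

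The article does not say how an intermediate-risk child enters the accuracy proportion, and it does not restrict the denominator to children given a low- or high-risk label.

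**The concern.** A child in the intermediate group has been labelled neither low- nor high-risk, so cannot have been wrongly given either label. Under the Methods wording that child counts towards accuracy. At a given error rate among the children a score does classify, the reported accuracy therefore rises as the score classifies fewer of them. This credits a property that the Introduction lists as a limitation of two widely used scores.

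The abstract's wording points the other way: a child must be correctly placed in the low- or high-risk group to count. At stake is the summary at published cutoffs for up to 30 scores, which the abstract names beside the AUC. Readers would compare those percentages between scores whose intermediate groups may differ widely, and between three-tier scores and any score with a single cutoff.

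**Working it through.** **Inputs.** The article gives no figure for the accuracy proportion, so there is none to reproduce. The planning numbers serve only to scale an example. The sample size section says "We aim to have a sample size of 2400 children" and "we estimate a true appendicitis rate of 30% in the multicenter study", and expects all scores to be calculable in at least half the cohort. That gives 2400 × 0.5 = 1200 children, 1200 × 0.30 = 360 with appendicitis (the article's own minimum of 360) and 1200 − 360 = 840 without. Intermediate shares and error rates are not given, so those below are assumptions.

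**Step 1: the two measures.** Let m be the intermediate share of all scored children, and e the error rate among those labelled low- or high-risk.

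- Methods wording: 1 − e(1 − m)
- Abstract wording, over all scored children: (1 − e)(1 − m)

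**Step 2: the difference.** 1 − e(1 − m) − (1 − e)(1 − m) = 1 − (1 − m) = m. The gap equals the intermediate share whatever e is. It is zero only if m = 0. If the denominator is instead limited to classified children, both wordings reduce to 1 − e.

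**Step 3: size, with e = 10% assumed.**

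| Intermediate share m | Methods wording | Abstract wording (all scored) |
|---|---|---|
| 0% | 90% | 90% |
| 20% | 92% | 72% |
| 40% | 94% | 54% |
| 60% | 96% | 36% |
| 80% | 98% | 18% |
| 100% | 100% | 0% |

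**Step 4: two invented scores on 360 children with and 840 without appendicitis.**

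| | Low | Intermediate | High |
|---|---|---|---|
| Score A, appendicitis | 18 | 54 | 288 |
| Score A, no appendicitis | 630 | 126 | 84 |
| Score B, appendicitis | 7 | 288 | 65 |
| Score B, no appendicitis | 160 | 672 | 8 |

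- Score A: intermediate 180/1200 = 15%. Methods: 1 − (18 + 84)/1200 = 91.5%. Abstract: (630 + 288)/1200 = 76.5%.
- Score B: intermediate 960/1200 = 80%. Methods: 1 − (7 + 8)/1200 = 98.75%. Abstract: (160 + 65)/1200 = 18.75%.

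B ranks above A on the Methods wording and far below it on the abstract's. With the denominator limited to classified children, A gives 918/1020 = 90% and B gives 225/240 = 93.75%, but B's figure describes only 240 of 1200 children. Whichever definition is used, the number cannot be interpreted without the intermediate share.

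**The case against.** The strongest reply is that this proportion decides nothing. The best score is the one with the highest AUC, and precision and power are planned on the AUC. The AUC depends on how a score orders children, not on where its tiers are cut. A reader might infer that the accuracy definition would steer the choice of score towards one with a large intermediate group. The article does not support that, because the selection rule does not use this measure.

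Other cutoff-based measures are also planned: sensitivity, specificity, predictive values, likelihood ratios and the missed-appendicitis rate. The low-risk misclassification rate is already defined, and the high-risk counterpart is one minus the positive predictive value at the high-risk cutoff. This stands, and it limits the harm. It does not remove it: the section lists no intermediate share for every score. Counts by risk group are planned only for the best-performing score. For the others a reader could work the share out only if sensitivity and specificity were given at both cutoffs.

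Three further inferences go too far. The abstract's line is not a formal contradiction, since it states no denominator and could mean the proportion correct among children labelled low- or high-risk. The Introduction does not call the intermediate group the main defect of the older scores; it is one of two limitations. The article also does not show that any ranking will reverse, because the splits above are invented. Finally, a non-misclassification rate is a coherent quantity, and counting intermediates as not correct is itself a choice. That is fair, but it does not make an unqualified non-misclassification rate, labelled accuracy, comparable across scores.

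**Conclusion.** The point holds as a should-fix. As worded, the Methods measure treats every intermediate-risk child as accurate. Over all scored children it exceeds the abstract's measure by exactly the intermediate share. That identity needs no assumption beyond the literal reading of the Methods sentence and a denominator of all scored children for both measures. The size for any actual score cannot be computed from the article, and the percentages shown rest on assumed splits.

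The fault is confined to the reported accuracy at published cutoffs for scores with an intermediate tier, and to comparisons involving them. The AUC analysis, the choice of best score, the sample size and data collection are untouched.

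**What to change.** Use one definition in both the abstract and the statistics section: accuracy = (low-risk children without appendicitis + high-risk children with appendicitis) / all children scored. State that intermediate-risk children stay in the denominator and are not counted as correct.

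Beside it, report for every score the intermediate proportion, the low-risk misclassification proportion and the high-risk misclassification proportion, each with its denominator. If all use the children scored as denominator, the four figures sum to 100%. The planned rate among children labelled low-risk can be kept as well. Settle the definition before accuracies are compared between scores, so that it is not chosen with the results in view.

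The cost is one reworded sentence and an extra column in the results table, with no new data. Reported accuracies for three-tier scores will look lower than under the present wording.
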